**Gaamo-V: Otootto Gobbara Higge Fulturo Leellanno Malaatta Buunxanni Borri-Xa’mo**

**Hajajo:** Konni woroonni shiqqino lamala borri-xa’mo illachishshannohu otootto gobbara higge fultino amuwira xa’minanninna bikkinanni xa’muuwaati. Doorshu noohu ( 0) kayse 4 geeshshaati. Muxxe tenne xiinxallo beeqqaancho, sa’u shoole lamallara me’’e hige malaatu macciishshamihero ballo eeggatena kulie? (keennanni gari : 0= horontanni dileellinoe malaatu sa’u shoole lamallara,, 1= keeshshe, 2= sae sae 3=roore yannanna 4= wo’ma woyte)

| **A.k** | **Leeltanno malaatta** | | **0**  Horontanni dileellanno | **1**  Keeshshe keeshshe | **2**  Sae sae | **3**  Roore yanna | 4  Wo’ma yanna |
| --- | --- | --- | --- | --- | --- | --- | --- |
|  | Ikkinorichi otoottote widoonni hige daynoha lawe macciishshaminoheni? | |  |  |  |  |  |
|  | Otootto xissitannohenni roorenkanni uurrutta yannara ? | |  |  |  |  |  |
|  | Mudukku woroonni ayirrannoherichi macciishshamannoheni? | |  |  |  |  |  |
|  | Hallikkira wori adda duunaminori woy ayirrinori macciishshame egenninoheni? | |  |  |  |  |  |
|  | Way shuma daggukkinni niixissannoheni? | |  |  |  |  |  |
|  | Way shuma gooffinokkiha lawe macciishshamannoheni? | |  |  |  |  |  |
|  | Jawiidi shuma gooffinokkiha lawe macciishshamannoheni? | |  |  |  |  |  |
|  | Aleenni xawinsiri giddo roorenkanni mittinsino qarri hiikkonneeti? (xa’mo 1–7) geeshsha | | ……………. | | | | |
|  | Mageshshi yanna mittu malaati macciishshamihe roorenkanni seeda yannara? | | ……… | | | | |
| **Kalqete Dhiwamaasinetenni Afi’nanni Babbaxxitino Borri-Xa’mo**  Konni woroonni no borri-xa’mo xa’minannihu goofimarchohooti. Xa’minannihu dhibbu malaati nooriranna nookkihuraati. Xa’minanni yanna lewu(6) agani gedensaanniiti | | | | | | | |
|  | Xagisi’ra hanafittankunni may soorro leeltinoha lawannohe? | 1= lowo geeshsha huroomma  2= woyyate  3= dhibbu ajanni ha’rinoe  4 = mitte soorro dino  5= shiima geeshsha xissanni nooe  6= xissanni nooe  7= lowo geeshsha xissanni nooe | | | | | |

**Gaamo-VI: mudukkunna sirote bisi qarqari bisu xe’ne daafira xa’manni borri-xa’mo (PFDI-20)**

**Hajajo: Konni woroonni noo xa’mora dawaro dawari; ha’runsote/buuxote xa’mo gedensaanni**. Xa’minannihu helleete ,ufuuffaate, sirote bisi qarqari malaattanna mageeshshi geeshshi mittimmansa, buunxanni borri-xa’mo. Dawarratta woyte sasu(3) agani aleenni ikkinoheri qaagi!. **0 = dino malaatu, 1= wo’manka woyte dikkino,** 2**=shiima yanna 3 =mereerimunni nna 4 = horontanni shiima yanna**

**Mudukkunna sirote bisi qarqari bisu xe’ne daafira xa’minanni borri-xa’mo (PFDI-20)**

| 1. ***K*** |  | **Dee’ni** | **Ee** | | | |
| --- | --- | --- | --- | --- | --- | --- |
|  |  | 0 dino malaatu | 1 wo’manka woyte dikkino | 2 shiima woyte | 3 mereerimunni | 4 horontanni shish  woyte |
|  | Godowikkira woriidi qarqarira woroo qole xiwannori hee’ranno? |  |  |  |  |  |
|  | Siimu qarqarira ayirre macciishshame egenninohe? |  |  |  |  |  |
|  | Otoottote widoonni ikkinorichi fulanni nooha lawannohe gede ikkannohe? |  |  |  |  |  |
|  | Otoote woy jawa shuma fultanno qoxxeessa xiwannori no gede macciishshamannohe? |  |  |  |  |  |
|  | Way shuma gooffinokkiha lawe macciishshamannohe? |  |  |  |  |  |
|  | Shumaa’ratta yannara xiwannoheri nooha lawannohe otoottokkira/qubbichikkinni kisse egennoottanni? |  |  |  |  |  |

**Helleetenna Xuuxxote Xiwani Daafira Xa’minanni Borri-Xa’mo (CRAD-8)**

|  |  |  |  |  |  |  |
| --- | --- | --- | --- | --- | --- | --- |
|  | Jawa shumara ofolatta woyte niixisannoheni? |  |  |  |  |  |
|  | Jawa shumara ofolte ka’eennano gooffinokkiha lawe macciishshamannoheni? |  |  |  |  |  |
|  | Jawa shuma ate hajajo gobbaanni fultannoheni? |  |  |  |  |  |
|  | Deeo ikkiro, ate hajajo gobbaanni fulannohe? |  |  |  |  |  |
|  | Fooleessu /fuuto ate hajajo gobbaanni fultannoheni? |  |  |  |  |  |
|  | Jawa shumara ofollatta woyte xissannoheni? |  |  |  |  |  |
|  | Jawa shuma mudditannoheni lowo geeshsha ? |  |  |  |  |  |
|  | Hellee gobbara higge fultannoheni deeu gedensaanni? |  |  |  |  |  |

**Way Shuma Mitiimma Daafira(UDI-6)**

|  |  |  |  |  |  |  |
| --- | --- | --- | --- | --- | --- | --- |
|  | Wayi shuma shumaa’ratta yannara macciishshamannoheri nooni? |  |  |  |  |  |
|  | Shuma ciphi-ciphi yitannohe muddite? |  |  |  |  |  |
|  | Shuma ciphi-ciphi yitanno, buusatta, hanxishshi’rattanna woy oso’litanna? |  |  |  |  |  |
|  | Shiima shuma ciphi-ciphi yitanno)? |  |  |  |  |  |
|  | Way shuma shumaadhe kaittarono gooffinokkiti macciishshantannohe? |  |  |  |  |  |
|  | Mudukku woridinna siimu qarqarira fayyimma dimacciishantannohe? |  |  |  |  |  |

**Gaamo-VII: Kalqete Shuma Cophi Yitanno Gara Xiinxallinanni Gade Borri-xa’mo**

**Hajajo:**

Lowo manni way shuma ciphi-ciphi assanno. Tenne xiinxallo umi mageeshshi manni shumansa ciphi- ciphi assannonna mittii’manno yaateeti. Ballo, sa’u shoole lamallara me’’e hige ciphi -ciphi assittaro hedi mereerimunni?

| A.K | Xa’mo | Dawaro |
| --- | --- | --- |
|  | Me’’e higge way shuma ciphi yaatta? | 1. =horontanni 2. = mitte hige lamalate gido. 3. = 2-3 geeshsha mitte lamela gido. 4. = mitte hige barrunni. 5. = Duucha hige mittu barri giddo 6. =wo’ma woyte. |
|  | Mageeshshi shuma ciphi assatta? | 0 = horontanni  2 = shiima  4 = Mereerima.  6 = lowota |
|  | Xaphoomunni, mageeshshi shuma barrunni ciphi assatta? (0 nna 10 mereero qoqqowi | 0 1 2 3 4 5 6 7 8 9 10 (taltino dawaaro qoqqowi.) |
|  | Mamoote way shuma ciphi yitannohehu? (taltino dawaaro dori) | 0 =horontanni diyitanno  1 = shumate minira ha’rammara albaanni.  2=buuseemma/hanxishshi’reemma yannara  3 = goxe he’reenna.   1. = looso looseemma woyte.   5 Shumaa’re kaeemma woytenna uddi’re kaeemma woyte  6 =Korkaatiweello.  7 = Wo’ma woyte. |

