Other pelvic floor disorders, including bladder and bowel symptoms, will be assessed using the International Consultation of Incontinence Questionnaire-Short Form (ICIQ-SF) ([143](#_ENREF_143)) and the Pelvic Floor Disability Index (PFDI-20) ([144](#_ENREF_144)). The International Consultation of Incontinence Questionnaire-Short Form (ICIQ-SF) is a four-item, disease-specific tool that assesses the symptoms and quality of life of patients with urinary incontinence. The four items are pertaining to the frequency of leakage, amount of leakage, interference with everyday life, and the perceived cause of leakage. Each item has its own response scale, and the total score is calculated as the sum of the first three items (relating to frequency, volume of leakage, and interference with everyday life). It is treated as a continuous scale with a possible range from 0 to 21, with the higher scores indicating worse symptoms ([87](#_ENREF_87)). The Pelvic Floor Disability Index (PFDI-20) consists of 20 items that contain three subscales: Pelvic Organ Prolapse Distress Inventory-6 (POPDI-6), Urinary Distress Inventory-6 (UDI-6), and Colorectal-Anal Distress Inventory-8 (CRADI-8). Each item has a response of either no (0) or yes (1) depending on the absence or presence of a complaint. If answered yes, the level of discomfort will be rated as 1 = unimportant, 2 = a little, 3 = moderate, or 4 = a lot. Both of these tools will be translated into the local language and translated back to English to check their consistency. The participants will be asked how often they have had the symptoms in the last three months.

To diagnose and quantify the stage of the prolapse objectively, a ruler marked with a centimeter will be used to measure the prolapse of nine points in and around the vagina. In addition, a weight scale and meter marked in centimeters will be used to measure a women’s weight and height to know her Body Mass Index.

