## Data Source and Measurement

Data on socio-demography (age, level of education, occupation, permanent place of residence religion, and ethnicity), obstetric and gynecologic history (number of childbirth, age at first marriage and childbirth, mode of delivery) will be recorded based on participants’ self-response to each question.

To diagnose POP symptomatically, the total score of the seven items with a five-point Likert scale will be calculated by summing up all responses and the total score will range from 0 to 28. If the participants' total response score is different from zero, she will be considered as having symptoms of prolapse. The Pelvic Floor Disability Index (PFDI-20) will be measured for each component separately. The average score of each subscale will be computed and multiplied by 25 to convert each subscale score between zero and 100. The overall scale score of the three-component will range from zero to 300. The higher values indicate the worst prolapse symptoms ([144](#_ENREF_144)).

To objectively diagnose POP, there are nine measurement points in the POP-Q system. All are measured at maximum Valsalva, except Total Vaginal Length (TVL) which is measured at rest. Measurements are expressed in centimeters to the nearest 0.5cm. These measures are translated into a staging system as described below (Table 2) ([6](#_ENREF_6), [12](#_ENREF_12), [123](#_ENREF_123)). The nine measurement points in and around the vagina are: Genital Haitus (GH) measured from the middle of the external urethral meatus to the posterior aspect of the hymenal remnant, perineal body (PB) measured from the posterior aspect of the hymenal remnant to the middle of the anal opening, point C is the lowest part of cervix and point D is the insertion of uterosacral ligaments to the cervix. Both points are measured relative to the plane of hymenal remnants. A hymenal remnant is chosen as it is a clearly defined and easily identifiable structure. Total vaginal length is measured from Hymenal remnant to point D (Point C will be used in post-hysterectomy patients). Point Aa is an arbitrary fixed point on the anterior vaginal wall, which is 3cm back from the middle of the external urethral meatus in normal cases. Point Ba is the lowest part of the upper anterior vagina. This point is not a fixed point like Aa. It can be anywhere along the vaginal wall above the first 3cm (Aa). Point Ap and Bp are similar points to Aa and Ba but found on the posterior vaginal wall.

.

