**Part-VII: The International Consultation on Incontinence Questionnaire**

**Instructions:**

Many people leak urine some of the time. This study is aimed to find out how many people leak urine and how much this bothers them. Please answer the following question, thinking about how you have been, on average, in the last four weeks.

| S.No | Questions | Responses |
| --- | --- | --- |
|  | How often do you leak urine? | 1. = never 2. = once a week 3. = 2-3 times a week 4. = once a day 5. = several times a day 6. = all the time |
|  | How much urine do you usually leak? | 0= none  2 = a small amount  4 = a moderate amount  6 = a large amount |
|  | Overall, how much does leaking urine interfere with your everyday life? (give a value between 0 (not at all) and 10 (a great deal) | 0 1 2 3 4 5 6 7 8 9 10 (encircle the appropriate number) |
|  | When does urine leak? Select all that apply to you | 0 = never leak  1 = before getting to the toilet  2 = leaks when coughing or sneezing  3 = leaks when sleeping  4 = leaks when exercising  5 = leaks when finished urinating and dressing  6 = leaks for no reason  7 = leaks all the time |

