**Gafa Mite: Dawaraanchote Dagoomittete Haja Xa’mi’nanni Borri-xa’mo**

Worada_________ Ollaa________ Dargu Kiiro____________ Koodde_____ Mobayle______________________

| **A.K.** | | **Xa’mo** | **Dawaro** | **Sai** |
| --- | --- | --- | --- | --- |
|  | | Dirikki me’’eho ? | __________wo’mu dirrinni wori |  |
|  | | Teessokki hiikkooti? | - - - 1. Quchumaho       2. Baadiyye |  |
|  | | Adhammete Gara | 1. Leexa 2. Adhantinota 3. shiidhinota 4. tidhantinota 5. baxxitinote |  |
|  | | Ammanokki hiitteeti?  (dawarokki qoqqowi? | 1. Ortodokise 2. Pirotestaante 3. Musiliime 4. Kaatolike 5. Wole xawisi____________ |  |
|  | | Loosu Qeecha? | 1.. Minaama (mini ama )  2. Baatto loossi’re galinoha   1. Mootimmate Loosaasincho 2. Mootimmannita ikkitinokki uurrinshara 3. Halanyaho 4. Rosaanchoho 5. Wole xawisi____________ |  |
|  | | Hiikko ayiddeeti?/ Hiitte gosaati? | 1. Sidaama 2. Wolayitta 3. Amaara 4. Guraage 5. Oromo 6. Wole xawisi___________ |  |
|  | | Rosikki deerri hiikkonneeti?? | 1. Nabbawanna borreessa didandeemma 2. Nabbawanna borreessa calla dandeemma 3. Umi dirimi rosaanchooti 4. 2^ki^ dirimi rosaanchooti 5. 5. 2^ki^ dirimi aleenni rosinote |  |
|  | | Gashshaniki rosi deerri hikkonneeti?  Adhantinota ikkituro,(xa’mo 103 buuxxi) | - - - 1. Nabbawanna borreessa didandaanno  1. Nabbawanna borreessa calla dandaanno 2. Umi dirimi rosaanchooti 3. 2^ki^ dirimi rosaanchooti 4. 2^ki^ dirimi aleenni rosinoho |  |
| **Gaamo-II: Heeshshote Gade Xa’minanni Borri-xa’mo**  Konni woroonni noo borri-xa’mo , xa’mitto/a gedensaanni taaltino dawaro qoqqowi | | | | |
|  | Mereerimunni, ayyirrinore me’’e saate bayiratta barrunni (waa, lowo qaqqo , haqqe, kinchonna gide | | -------- sate |  |
|  | Sigaara wiliishshite egennootta? | | 1. Dee’ni 2. Ee |  |
|  | Maatekki giddo otoottote ayyara gobbara higge fultinohu no ? | | 1. Dee’ni 2. Ee |  |
|  | Keeshshitino busano buuse egennota sase lamallara aleenni ? | | 1. Dee’ni 2. Ee |  |
|  | Jawa shumara ofolata woyte Fula giwanohenni? (fulate qarrissanno) | | 1. Dee’ni 2. Ee |  |
|  | Mundeekki giddo sukkaare noohero buuxi’rootta? | | 1. Dee’ni 2. Ee |  |

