**POP-Q:**

| Aa = | Ba = | C = |
| --- | --- | --- |
| Gh = | Pb = | TVL = |
| Ap = | Bp = | D = |

Otoottote doycho sentimetirenni wori! __________________________

Uurrite bussanni hedhenanni bikkinonni bikko: □ nose □ dinose qelpheepho(mL):______

**Gafa-X: Otootto Gobbara Fulturo Hiittoo Heshshote Gade Nooro Bunxanni Borri- Xa’mo (Otootto Gobbara Fultino Amuwira Calla)**

**Hajajo**: Konni woroonni noo malaati leellannohu otootto gobbara higge fultino amuwira leellanno malaateeti. Taaltino dawarora malaatisi.

| **Amado** | **Xa’muwa** | 0  Lowo geeshsha danchaho | 1  danchaho | 2  duushshanno | 3  diduushshanno | 4 lowo geeshsha didushshanno |
| --- | --- | --- | --- | --- | --- | --- |
| XAPHOOMU FAYYIMMA(GHP) | Fayyimmakki hiittoonni xawisatta? |  |  |  |  |  |
|  |  | **0 wo’ma woyte dikkino** | **1 shiima yanna** | **2 mereerimunni** | **3 lowo geeshsha** |  |
|  | Otootto gobbara higge fulate mitiimma heeshshokkira. |  |  |  |  |  |
| MINI LOOSO LOOSA HOOGA HOGGAolhlimitations | Otootto gobba higge fultinohe dafira, mini loosi hittoo mitiimma abbinohe? |  |  |  |  |  |
|  | Otootto gobba higge fula ,mini gobbayidi loosikkira mitiimma abbinohe? |  |  |  |  |  |
| Mannu noowa ha’ra hoogate qarra | Otootto gobba higge fulte milli yaattata mitiinsinoheni? |  |  |  |  |  |
|  | Otootto gobbara higge fultannohe baychunni baycho hodhate mitii’mitanni? |  |  |  |  |  |
|  | Otootto gobba higge fultino daafira,dagoomu ledo xaadate mitii’mitta? |  |  |  |  |  |
|  | Otootto gobba higge fultinohe daafira miillaki ledo xaadate mitii’mitta? |  |  |  |  |  |
| Mannu ledo gade ledo | Otootto gobba higge fultinohe daafira,maatekkira mitiimma abbinoheni? |  |  |  |  |  |
|  | Otootto gobba higge fultino daafira siimu xaadooshshira mitiimma abbinohe? |  |  |  |  |  |
|  | Otootto gobba higge fultino daafira,maatekkira mitiimma abbinohe? |  |  |  |  |  |
| Akata | Otootto gobba higge fultino daafira,dadillu macciishshamannoheni? |  |  |  |  |  |
|  | Otootto gobbara higge fultino daafira caaccawaatani? |  |  |  |  |  |
|  | Otootto gobba higge fultino daafira ate bunshe macciishshantannoheni? |  |  |  |  |  |
| Goxichu/wolqa | Otootto gobba higge fultino daafira goxatta woyte mitii’mitta? |  |  |  |  |  |
|  | Otootto gobba higge fultinohe daafira bunshe calla macciishshantannohe? |  |  |  |  |  |
| Marichi qaafo adhita?taken | Hocoota/pade horonsiraata. |  |  |  |  |  |
|  | Otootto gobba higge fultanno yannara xiibbe egennootta? |  |  |  |  |  |

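### The annexed Sidaamu Afoo ICIQ-SF item 3 asks about leak volume per day instead of interference with daily life, and the top PFDI-20 label does not clearly express the highest bother

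*Protocol*

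**What the plan says.** Paper II (Data Collection Tools and Procedures) uses the ICIQ-SF and the PFDI-20 to describe other pelvic floor disorders.

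- **ICIQ-SF scoring.** The protocol states that "the total score is calculated as the sum of the first three items (relating to frequency, volume of leakage, and interference with everyday life"), with a range of 0 to 21.
- **ICIQ-SF item 3, English (Annex II, Part VII).** "Overall, how much does leaking urine interfere with your everyday life", answered from 0 to 10 with both ends labelled.
- **ICIQ-SF item 3, Sidaamu Afoo (Annex-III, Part VII).** "Xaphoomunni, mageeshshi shuma barrunni ciphi assatta", answered from 0 to 10 with neither end labelled.
- **PFDI-20 scoring (Paper II, Data Source and Measurement).** "The average score of each subscale will be computed and multiplied by 25 to convert each subscale score between zero and 100". The three subscales sum to 0 to 300, and higher means worse.
- **PFDI-20 category 4.** The label is *quite a bit* in Annex II and *a lot* in the Paper II text. In the Sidaamu Afoo instruction line (Annex-III, Part VI) it is "4 = horontanni shiima yanna".

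Both tools are to be translated and back-translated. Paper II (Data Quality Assurance) adds a pretest of the tools other than the POP-SS on 41 women.

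**The concern.** The Sidaamu Afoo form is the one interviewers will read aloud. If item 3 asks a second volume question, the ICIQ-SF total lacks one of its three stated components, although it still runs from 0 to 21 and looks normal. Nothing in the data would show the substitution, and the missing answers could not be recovered after fieldwork.

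For the PFDI-20, the top category of all 20 items carries the largest score. If its label does not read as the highest bother, a woman with severe bother may have no category that plainly fits her.

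**Working it through.** **Item 3, from the form's own parallel text.** No outside knowledge of the language is needed.

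1. Sidaamu Afoo item 2, the volume question, reads "Mageeshshi shuma ciphi assatta". Its English counterpart asks how much urine is usually leaked.
2. Item 3 consists of those same words plus *Xaphoomunni* and *barrunni*.
3. *Xaphoomu* heads the general-health domain in the Annex-III quality-of-life section, so *Xaphoomunni* corresponds to the English *overall*.
4. *Barrunni* means per day. The heavy-carrying item has "saate bayiratta barrunni" where the English asks for hours per day, and ICIQ-SF item 1 uses *barrunni* for once a day.
5. The form has words for the missing idea. The quality-of-life items use *mitiimma* where the English says affect, as in "mini loosi hittoo mitiimma abbinohe". The Part VII introduction has a related form, *mittii'manno*, where the English speaks of bother. No such word appears in item 3.
6. The English labels for 0 and 10 are not carried over. The woman is only asked to choose between 0 and 10.

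**Weight of item 3 in the total.**

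- Item maxima: 5 (item 1, coded 0 to 5), 6 (item 2) and 10 (item 3).
- Stated range reproduced: 5 + 6 + 10 = 21.
- Share of item 3: 10 / 21 = 0.476, or 48%.
- Points left for frequency and volume as intended: 5 + 6 = 11.
- Points resting on volume wording if the form is used as printed: 6 + 10 = 16 of 21.

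The response list of item 1 appears numbered 1 to 6 in both languages. This may be a list-numbering artefact, so it is not counted and 0 to 5 is assumed.

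**PFDI-20 category 4.**

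1. In the instruction line, category 2 is *shiima yanna*. Category 4 is the same two words with *horontanni* in front.
2. *Shiima* stands for a small amount in ICIQ-SF item 2, and *shiima yanna* is the quality-of-life label for *slightly*.
3. *Horontanni* stands for never or none in the ICIQ-SF. In Part III it renders *permanently* (menstruation stopped for good). The documents never translate the combination *horontanni shiima*.
4. The table header gives category 4 a different wording, *horontanni shish woyte*, which looks broken. That may be a typing or extraction fault.
5. For *a lot*, the quality-of-life section uses *lowo geeshsha*. It is not used here.

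Stated range reproduced: 4 × 25 = 100 per subscale, and 3 × 100 = 300. One category step on one item moves a six-item subscale by 25 / 6 = 4.2 points and the eight-item subscale by 25 / 8 = 3.1 points. How many women would shift, and in which direction, is not in the documents.

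**The case against.** **Checks still to come.** Back-translation is written as a future step, and nothing says the annexed form has been through it. A missing interference question is what back-translation should reveal. This stands as a reason for moderation, but the form as annexed still needs correcting. The pretest looks at clarity and interview time. Item 3 is a clear question, only the wrong one, so it could pass.

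**Low stakes for the trial.** Paper II's primary outcome is anatomical prolapse. Neither score is among its listed independent variables, nor among the covariates of Papers III and IV. The trial outcomes are the POP-SS, the P-QoL components and the two global-impression items. This stands in full.

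**The PFDI-20 label.** A reader might infer that category 4 says *very little time* and so reverses the scale. The documents do not support that. *Horontanni* has more than one rendering, the header differs, and the categories are numbered upwards with *mereerimunni* (moderately) at 3, read out by fluent interviewers. What remains is that the label contains the label of category 2 and does not clearly name the highest bother.

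**Both totals simply wrong.** A reader might also infer this, and attach figures such as 225 in place of 300 for a woman who avoids category 4 on every item. The arithmetic rules and ranges are right, and such figures assume a response pattern on which the documents give no data.

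**Conclusion.** The ICIQ-SF point is established by the parallel forms: item 3 in Annex-III asks for volume, not interference, and lacks its anchors. If the form is used as printed, 10 of 21 points (48%) do not measure what the scoring rule names. This assumes item 1 is coded 0 to 5.

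The PFDI-20 point is smaller. The category 4 label is unclear as the top of a bother scale and inconsistent within the form. Its meaning needs a Sidaamu Afoo speaker, and no error size can be given.

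Both are faults in what the scores would mean, not in how they are calculated. Their reach is limited to the descriptive pelvic floor scores of the Paper II survey. No trial effect estimate and no prolapse prevalence estimate depends on them.

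**What to change.** Before Annex-III is printed:

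1. Replace Sidaamu Afoo ICIQ-SF item 3 with a translation of the English interference question, and restore the labels for 0 (*not at all*) and 10 (*a great deal*).
2. Reword PFDI-20 category 4 as the highest bother, identically in the instruction line and the table header. The form's own *lowo geeshsha* is a candidate, to be confirmed by a speaker.
3. Settle the English label for category 4, which is *a lot* in Paper II and *quite a bit* in Annex II.
4. Name both items as specific checks in the back-translation already planned.

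The cost is a few wording edits and a speaker's confirmation. Sample size, scoring rules and analysis do not change.

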**GaamoVIII: Fesitullu Qarri Noo Amuwira Xa’minanni Borri Xa’mo**

| A.K | Xa’mo | Dawaro |
| --- | --- | --- |
|  | Keeraancho ila ilte egennootta? | 0 = Dee’ni 1= Ee |
|  | Mitto barranna hashsha sa’e gama’mite egennootanni? | 0 =Dee’ni 1= Ee |
|  | Duucha woyte ciphi yitannohenni? | 0 =Dee’ni 1 =Ee |

**Gafa-IX: Otootto Gobba Higge Fultinotta Bikkinanni Gade (POP-Q)** (horoonsi’nannihu hikkimannaahooti)

**Hajajo:**:Honsu gari bikkote gade noose (POP-Q). mannimmate guunte/biso milli assinanni loossinsanni bikkinanni. Bikkinannihu seentimetiretenniiti

Hojja: ____________________ cm

Qelpheepho/ayirrinye: ____________________ kg

Godowaho malaatu leella: ­­­­­­­­­­­­­­ □ Ee □ Dee’ni

